# Protocol for a phase III RCT and economic analysis of two exercise delivery methods in men with PC on ADT

**DOI:** 10.1186/s12885-018-4937-x

**Published:** 2018-10-23

**Keywords:** Prostate cancer, Androgen deprivation therapy, Exercise, Randomized controlled trial, Quality of life, Fatigue, Physical fitness, Cost-effectiveness, Patient adherence

## Abstract

**Background:**

Androgen deprivation therapy (ADT) is commonly used to treat prostate cancer. However, side effects of ADT often lead to reduced quality of life and physical function. Existing evidence demonstrates that exercise can ameliorate multiple treatment-related side effects for men on ADT, yet adherence rates are often low. The method of exercise delivery (e.g., supervised group in-centre vs. individual home-based) may be important from clinical and economic perspectives; however, few studies have compared different delivery models. Additionally, long-term exercise adherence and an understanding of predictors of adherence are critical to achieving sustained benefits, but such data are lacking. The primary aim of this multi-centre phase III non-inferiority randomized controlled trial is to determine whether a home-based delivery model is non-inferior to a group-based delivery model in terms of benefits in fatigue and fitness in this population. Two other key aims include examining cost-effectiveness and long-term adherence.

**Methods:**

Men diagnosed with prostate cancer of any stage, starting or continuing on ADT for at least 6 months, fluent in English, and living close to a study centre are eligible. Participants complete five assessments over 12 months (baseline and every 3 months during the 6-month intervention and 6-month follow-up phases), including a fitness assessment and self-report questionnaires. Biological outcomes are collected at baseline, 6, and 12 months. A total of 200 participants will be randomized in a 1:1 fashion to supervised group training or home-based training supported by smartphones, health coaches, and Fitbit technology. Participants are asked to complete 4 to 5 exercise sessions per week, incorporating aerobic, resistance and flexibility training. Outcomes include fatigue, quality of life, fitness measures, body composition, biological outcomes, and program adherence. Cost information will be obtained using patient diary-based self-report and utilities via the EQ-5D.

**Discussion:**

To disseminate publicly funded exercise programs widely, clinical efficacy and cost-effectiveness have to be demonstrated. The goals of this trial are to provide these data along with an increased understanding of adherence to exercise among men with prostate cancer receiving ADT.

**Trial registration:**

The trial has been registered at clinicaltrials.gov (Registration # NCT02834416). Registration date was June 2, 2016.

**Electronic supplementary material:**

The online version of this article (10.1186/s12885-018-4937-x) contains supplementary material, which is available to authorized users.

## Background

Prostate cancer (PC) is the most common cancer in men [1, 2], affecting an estimated 21,600 Canadian men in 2016. With increased screening and better treatment of early disease, 10-year disease-specific survival has reached almost 95% [2]. This means that more men are living longer with PC, with many progressing to advanced disease over time. Androgen deprivation therapy (ADT), an effective treatment, blocks the production of testosterone, leading to apoptosis and decreased proliferation of PC cells. It has been used in advanced PC for 7 decades [3]. At present, almost 50% of men with PC can expect to receive ADT at some point after diagnosis [4–6]. Although ADT improves disease control and prolongs survival (often by several years) [7–9], it is associated with numerous adverse effects, predominantly due to depriving organs and tissues of testosterone. These adverse effects include worsening quality of life (QOL) and fatigue [10–13], significant declines in muscle mass and physical strength, loss of bone mineral density (BMD), and various metabolic side effects (e.g. increased blood glucose and cholesterol).

The effects of ADT on health-related QOL (hereinafter referred to as QOL), are diverse and persistent, including worse global QOL, worse physical function, more fatigue, poorer sexual function, hot flushes, and breast tenderness [14–24]. Some studies have reported worse social function [15] and mental well-being [15, 18]. These effects are typically seen within 3 to 12 months of ADT initiation [12] and persist or slowly worsen over the next 3 years with ongoing ADT use [25]. Such effects are profoundly disruptive to patients, spouses or partners, and families [10, 11, 26–28].

Multiple studies have reported reductions in overall muscle mass, upper and lower extremity strength, grip strength, and daily functioning in men on ADT [12, 24, 29–36]. Two studies suggested an increased risk of falls in men on ADT, most of whom are elders [37, 38]. Numerous studies have also shown reductions in BMD within 6–12 months of ADT initiation, with further declines with ongoing ADT use for at least 10 years [39–46]. Loss of BMD has been associated with a 40–60% increased risk of fracture [13, 47–50]. Finally, ADT has also been associated with increased fat mass, insulin resistance, increased blood glucose, and unfavourable alterations in lipids [34, 35, 51–55]. These metabolic changes are associated with an increased risk of diabetes [13, 56–58] and cardiovascular outcomes [13, 56, 57, 59–63], although the latter remains controversial [64, 65].

Exercise-based interventions have been shown in at least 14 clinical trials to ameliorate most of these adverse effects [30, 66–77]. As summarized in several recent systematic reviews [78–82], the benefits of exercise have been shown in interventions of 8 to 24 weeks’ duration, including improved general or overall QOL [30, 70, 74], prostate-specific QOL [30, 74], and fatigue [30, 66, 69, 70, 73, 74]. Exercise has also been associated with improved muscular endurance (upper body = 22–115%, lower body = 23–167%), increased maximal strength (upper body = 40%; lower body = 96%), increased quadriceps muscle thickness by 16%, preserved or improved total body lean mass, and prevention of fat gain [30, 68, 70, 73]. No other intervention has been shown to improve as many side effects of ADT.

Three small studies found preliminary evidence of benefits of exercise in insulin parameters, glucose, lipids, or inflammatory markers, but effects on BMD remain unclear [73, 74, 83]. These effects need to be confirmed in larger studies, given the potential benefits of preventing diabetes or reducing cardiac risk factors in older men on ADT, the majority of whom will die of heart disease rather than PC [84–91]. Importantly, there is a robust literature in the general population showing that exercise improves glucose [92–94], lipids [95], and BMD [96–98]. And regular exercise after a diagnosis of PC may be associated with improved survival [99].

Although multiple studies have demonstrated many benefits of exercise for men with PC on ADT, the strongest and most consistent benefits have been shown with 1:1 supervised (i.e. personal training), in-centre interventions [100]. As summarized in recent reviews [81, 82, 101], four trials have featured 1:1 supervised exercise interventions, all of which reported positive effects on QOL or fitness outcomes. Two studies (only one was randomized) were group-supervised interventions, and both showed benefits in QOL and/or fitness outcomes. In contrast, of the four home-based studies (two randomized controlled trials (RCTs)), only two were positive, and the magnitude and breadth of benefits were smaller than with supervised exercise interventions. Of note, these three exercise delivery models have not been directly compared to one another. Prior trials have used different outcome measures, assessment time points, and training routines, making indirect comparisons difficult.

Despite the accumulating evidence of benefits, few men with PC, including those on ADT, exercise regularly [99, 102–105]. For exercise interventions to be most useful to men on ADT, long-term exercise adherence and benefits must be achieved. Long-term exercise adherence has been defined as engaging in regular exercise for at least 6 months post-intervention [106]. In the general population, about 50% of individuals stop exercising after 6 months. Experience with cancer survivors suggests that they fare no better [107]. Cessation of exercise leads to loss of benefits in virtually every setting [108]. Unfortunately, most previous research in men on ADT has been limited to reporting exercise benefits and adherence only to the end of the supervised exercise intervention [79, 80]. In two studies examining participants 4–6 months post intervention, weekly exercise was reduced and QOL benefits were diminished over time [69, 74].

Relatively little is known about what factors are associated with adherence in this population. Only one study has formally examined adherence in an exercise intervention in men on ADT, finding that age, exercise stage of change, and intention were independent predictors of adherence [109]. However, only supervised in-centre exercise was examined and adherence was assessed only during the intervention phase. In summary, although adherence to exercise is crucial, little is known about adherence with different exercise delivery models and factors predicting adherence after the formal intervention phase in men on ADT. It is particularly important to identify factors that support long-term adherence, since men on ADT often continue this treatment for at least 2 to 3 years (and often indefinitely, depending on the indication).

Two other important barriers to exercise uptake relate to resources. First, despite its clinical value, no publicly funded exercise program exists in Canada for anyone with a cancer diagnosis, including men on ADT. This is likely due, in part, to the absence of any data on cost-effectiveness of exercise interventions in patients with PC. In contrast, cardiac rehabilitation is widely available and publicly funded because it has been shown to be both efficacious and cost-effective [92, 110]. Given increasing fiscal pressures, all levels of government are carefully evaluating both efficacy and cost-effectiveness of potentially insurable services.

Second, a related resource issue is alternate exercise delivery models. As outlined above, three main exercise delivery models have been studied in men on ADT – supervised 1:1, group-supervised, and home-based programs; however, our group has conducted the only clinical trial directly comparing 2 exercise delivery models (supervised 1:1 and group supervised) in men on ADT [77]. This trial was a pilot study that demonstrated the feasibility of enrolling patients into a RCT of different exercise modalities along with high intervention adherence and study retention [77]. However, multiple comparative trials have been conducted in other settings [111, 112]. For example, a systematic review of 12 RCTs of almost 2000 patients in cardiac rehabilitation has shown similar benefits of home-based versus in-centre rehabilitation on exercise capacity, cardiac events, modifiable risk factors (lipids, blood pressure, etc.), and mortality [112]. Of note, adherence was greater among home-based compared to in-centre participants in those studies. Clearly, both models require significantly fewer resources for population-level delivery than the gold-standard of 1:1 supervised, facility-based training. In addition, these models of exercise delivery may have added benefits such as improved adherence or social interaction, yet these modalities have never been effectively and directly compared for clinical efficacy or cost-effectiveness in men on ADT.

Given the gaps in the published evidence, we recently conducted a phase II trial to assess the feasibility and efficacy of these 3 delivery models in a 6-month intervention [113] (manuscript submitted). The preliminary results suggested that group-supervised exercise and home-based exercise were generally non-inferior to 1:1 supervised exercise for both QOL and fitness outcomes. Specifically, group-supervised exercise was shown to have less than a 20% probability of being inferior to 1:1 exercise for 2 of 3 QOL and 3 of 3 fitness outcomes. The home-based arm had less than a 25% probability of being inferior to the 1:1 arm for 1 of 3 QOL and 3 of 3 fitness outcomes. Moreover, the home-based arm was associated with the highest adherence based on accelerometry. Altogether, this provided a foundation to refine our phase II protocol and conduct the present phase III trial, in which we decided to directly compare 2 exercise delivery methods that are least resource intensive. Although efficacious, the 1:1 supervised intervention arm appeared to provide minimal benefit over a group-supervised program and is cost-prohibitive within a publicly funded health care system.

The primary aims of this phase III non-inferiority RCT are:i.To determine, in men with PC on ADT, whether a home-based supported exercise program is non-inferior to a group supervised in-centre (facility-based) exercise program on the primary outcomes of fatigue and functional endurance;ii.To examine adherence to exercise and predictors of adherence in each exercise group during the 6-month intervention and for 6 months after program completion;iii.To conduct an economic analysis comparing both exercise interventions and usual care.

## Methods

### Study design

This trial is a multi-centre, 2-arm non-inferiority RCT with blinded, validated, and clinically relevant outcome measures (Fig. 1). It will take place at two of Canada’s largest, university-affiliated cancer centres with large genitourinary site groups and significant RCT and exercise expertise: the Princess Margaret Cancer Centre (PM) in Toronto and the Tom Baker Cancer Centre in Calgary (TBCC). Participants will also be recruited from 2 community-based hospitals (in the Greater Toronto Area), Southlake Regional Health Centre and Scarborough and Rouge Hospital – Centenary site. Ethics approval has been obtained at all institutions. All study participants will provide written informed consent prior to study enrollment. Participants can voluntarily withdraw from the study at any time. Participants will be withdrawn from the study at the time of symptomatic disease progression. Any protocol amendments will be approved by the research ethics boards and communicated to investigators as well as to study participants as directed by the research ethics board. The trial is registered at clinicaltrials.gov (registration number: NCT02834416) and the SPIRIT figure is shown in Additional file 1.

**Fig. 1 Fig1:**
[figure not shown]
Study flow diagram

### Study participants

The trial will include men with histologically confirmed PC who are fluent in English, able to provide consent, live close to a study centre and are either starting or continuing on ADT for at least 6 months or those in an androgen-deprived (or castrate) state for the duration of the intervention (total testosterone < 1.7 nmol/L). Men are ineligible if they are already meeting guidelines for moderate to vigorous physical activity (MVPA) or have conditions that would interfere with ability to participate. Details are listed in Additional file 2: Table S1.

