##### Adherence

Program adherence and predictors of adherence will also be assessed. We recognize there is no perfect, all-inclusive definition of adherence. We will therefore measure different elements of adherence in this trial. Our primary adherence measure is the proportion of individuals in each arm who achieve at least 150 min of MVPA at both the three-month and six-month time points based on objective measurements via accelerometry. A target of 150 min is recommended by both Cancer Care Ontario’s guideline for cancer survivors [117] and the revised Canadian Society for Exercise Physiology (CSEP) guideline for adults and older adults [156]. Recognizing limitations of accelerometry (e.g. technical malfunction, incomplete wearing, not capturing all activities) we will also capture self-reported MVPA with the Godin Leisure Time Exercise Questionnaire (GLTEQ) at each time point. The GLTEQ is a brief, self-administered validated questionnaire that records light, moderate, and vigorous exercise performed each week in 15-min increments [157, 158]. For those in the group supervised arm, we will capture weekly attendance at exercise sessions. For those in the home-based program, we will measure three elements of adherence/engagement: a) Fitbit step counts; b) frequency of health coach contacts; c) frequency of use of the smartphone app.

Study participants will be asked to wear Actigraph GT3X (Pensacola, FL) accelerometers daily from awakening to bedtime for 1 week at each assessment time point (including baseline). Accelerometers are reliable [159] and non-obtrusive, and capture all physical activity during waking hours, thereby providing information on total physical activity during the time period of observation [160]. Accelerometer data will be extracted in 60-s epochs and screened using standard methods for: (i) at least 4 days of valid data, including (ii) at least 10 h of wear time per day; (iii) continuous non-wear time (periods of time with zero movement counts per minute) of more than 1 h. Total time spent in MVPA (> 1952 movement counts per minute [161]) will be calculated for the week. Additionally, accelerometer data enables the capture of sedentary behaviour using a protocol of time spent in activities with < 100 counts per minute and time spent inclined (using the inclinometer setting).

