#### Adherence

Several analyses will be used to assess adherence to the exercise programs and the relationship of adherence to both time and potential predictors. Adherence will be defined as a binary variable for the primary analysis, which uses accelerometry to measure MVPA. We will assess adherence over 4 distinct periods: 0–3 months, 3–6 months, 6–9 months and 9–12 months, so that each subject has up to 4 observation periods for adherence-based analyses. Our first analysis of adherence will simply be the calculation of percentages adhering in each group in each of the 4 time windows. Chi-squared or Fisher’s exact tests will compare adherence across groups within each of the time windows. All further analyses will be done on the sequence of 4 adherence measures on each subject using a generalized estimating equation (GEE) logistic regression model with an AR1 correlation structure.

Predictors of adherence will be examined at the exosystem, mesosystem, and microsystem levels using specific questionnaires as detailed earlier. These will be considered for inclusion in models examining each of the adherence variables separately. Mediation/moderation analyses will be explored based on the primary findings.

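### The adherence analyses leave out baseline accelerometer MVPA and the stratification factors, which costs precision between arms and can confound the predictors of adherence

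*Protocol article*

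**What the plan says.** All references are to the protocol article.

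- **Study participants:** "Men are ineligible if they are already meeting guidelines for moderate to vigorous physical activity (MVPA"). How this is measured at screening is left to Additional file 2, which is not shown.
- **Outcomes and measures, Adherence:** the primary adherence measure counts men "who achieve at least 150 min of MVPA at both the three-month and six-month time points based on objective measurements via accelerometry". This is a level reached, not a change from entry. Participants wear "accelerometers daily from awakening to bedtime for 1 week at each assessment time point (including baseline"), so a baseline value on the same instrument exists.
- **Randomization:** allocation follows the baseline assessment and is stratified on centre and prior ADT duration (under 3 months against 3 months or more).
- **Statistical analysis, Adherence:** "Adherence will be defined as a binary variable for the primary analysis, which uses accelerometry to measure MVPA". Percentages are calculated in four windows, and chi-squared or Fisher's "exact tests will compare adherence across groups within each of the time windows". Further analyses model the four values per man "using a generalized estimating equation (GEE) logistic regression model with an AR1 correlation structure". The only candidate covariates named are the exosystem, mesosystem and microsystem predictors, and prior MVPA is not one of them.
- **Contrast:** the co-primary ANCOVA adjusts for the baseline value and both strata, and the mixed models for the secondary outcomes add both strata.

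**The concern.** An endpoint defined as reaching a fixed level depends on where a man starts. Even after men at guideline level are excluded, those who enter can range from almost no MVPA to just under 150 min, and those near the threshold need to change least to be scored adherent. The trial measures that starting point with the same device, yet no adherence analysis names it.

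Two things are at stake.

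1. **The arm comparison.** Variation in later MVPA that baseline MVPA could explain is left as noise. A chi-squared or Fisher test cannot take a covariate, so adjusting means replacing the stated test, not merely filling in detail.
2. **The predictor analyses.** Motivation, planning, relatedness and neighbourhood walkability were not randomized, and each may be associated with activity before entry. Without baseline MVPA in the model, a variable can look like a predictor of adherence to the programme when it only marks men who were already more active. Predictors of adherence are part of primary aim (ii), and the Discussion intends the findings on psychological predictors as a basis for future intervention studies.

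**Working it through.** **The plan's own figure.** The only stated power is 81% for FACT-F and 6MWT with 100 per arm. The margin and SD are in Additional file 4, which is not shown, so it cannot be reproduced. Back-solving at one-sided 0.025 gives margin/SD = (1.96 + 0.878) × √(2/100) ≈ 0.40. This has no bearing on adherence, for which the article gives no rate, power or sample size.

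**Inputs from the article.** 200 men, 1:1; cut-off 150 min MVPA; unadjusted test within a window; strata of centre and ADT duration.

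**Assumed inputs (none is in the article).**
- Baseline log-MVPA is normal with mean log(80) and SD 0.8, screened at 150 min, either exactly or with a log-scale screening error of SD 0.5.
- Follow-up log-MVPA has mean log(140) in one arm and is higher by 0.4 in the other. Its SD within arm is 0.8 before the strata.
- Four strata with weak effects, spaced 0.1 apart on the log scale.
- Baseline-to-follow-up correlation of 0.3, 0.5 or 0.7.

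The implied adherence rates follow from the total SD √(0.64 + 0.0125) = 0.808:
- Lower arm: P(Z > ln(150/140)/0.808) = P(Z > 0.085) ≈ 47%.
- Higher arm: P(Z > (0.069 − 0.4)/0.808) = P(Z > −0.410) ≈ 66%.

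**Method.** 1,500 simulated trials per setting, two-sided 5%. The unadjusted chi-squared test is set against logistic regression with baseline log-MVPA, and against the same model with the strata added. One follow-up window is simulated, as in the stated per-window test. The Monte Carlo standard error is about 1.0 point for power near 80% and 0.6 points for size near 5%. The tests are compared on the same simulated trials.

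**Power with a true arm difference.**

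| Correlation | Screening | Unadjusted | + baseline MVPA | + baseline MVPA and strata | Total gain (points) |
|---|---|---|---|---|---|
| 0.3 | exact | 77.9% | 78.5% | 79.0% | 1.1 |
| 0.3 | with error | 80.1% | 81.1% | 81.3% | 1.2 |
| 0.5 | exact | 79.1% | 85.2% | 85.2% | 6.1 |
| 0.5 | with error | 80.3% | 84.7% | 85.7% | 5.4 |
| 0.7 | exact | 76.5% | 90.0% | 90.3% | 13.8 |
| 0.7 | with error | 77.7% | 91.7% | 91.7% | 14.0 |

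The strata add between 0 and 1.0 point once baseline MVPA is in the model.

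**As extra men.** The ratio [(1.96 + z(adjusted power)) / (1.96 + z(unadjusted power))]² gives:
- 1.03 at correlation 0.3;
- 1.16 to 1.18 at 0.5;
- 1.48 to 1.51 at 0.7.

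A separate simulation with other assumed inputs, using the marginal difference in proportions, gave gains equivalent to about 16-19% more men at 0.5 and 42-49% at 0.7.

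**Size with no true difference.** The unadjusted test rejected in 4.8% to 5.5% of trials and the two adjusted tests in 4.1% to 5.3%. The planned test has no false-positive inflation.

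**Men already at or above 150 min at baseline.** The share is 0% with exact screening, about 7% with the screening error above, and 15-18% in the separate simulation, which assumed self-report screening correlated 0.3-0.5 with accelerometry. The article does not say which case applies.

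**Predictor analyses.** No figure is offered here. The argument is structural: the endpoint is a level, the candidate predictors are not randomized, and entry MVPA is not named as a covariate.

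**The case against.** **The exclusion already deals with prior activity.** This stands as far as the eligibility criterion goes. Excluding men at guideline level is a safeguard and does not conflict with the adherence measure. A reader might infer that activity present before entry is simply counted as adherence. The article does not support that as a finding: it would require screening that misclassifies men against accelerometry, and the screening method is not shown.

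**Randomization removes any bias between arms.** This stands. A reader might infer that the arm difference is distorted by prior activity. It is not: baseline MVPA is balanced in expectation, and chance imbalance is sampling error that the test already allows for. For the arm comparison the issue is efficiency only.

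**Covariates for the GEE belong in the full analysis plan.** This stands in part. The article gives no closed covariate list for the GEE, and predictors are only candidates for inclusion. The chi-squared or Fisher comparison, however, is stated, and it is unadjusted.

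**The gain may be small, and adherence is not a powered contrast.** Both are fair. At correlation 0.3 the gain is about 1 point, and the article gives no correlation. Aim (ii) is to examine adherence and its predictors in each group, not to test a confirmatory contrast. But the data are already collected, so even a modest gain costs little, and the problem with the predictors does not depend on power.

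**Conclusion.** The point holds as one of lost precision and of interpretation, not of bias. As written, the between-arm adherence test is unadjusted, and no adherence analysis names baseline accelerometer MVPA or the strata, unlike the co-primary analysis (baseline and strata) and the secondary-outcome models (strata). Under the assumed inputs the cost is about 1, 5-6 and 14 power points at correlations 0.3, 0.5 and 0.7, nearly all of it from baseline MVPA. The case for the strata is consistency with the design and the other models rather than power. The consequence for the predictor analyses is not quantified, but it does not depend on how men were screened, because exact screening still leaves a wide range of entry activity below 150 min. The change is worth making, since adherence and its predictors form a primary aim.

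**What to change.** In the Adherence part of the statistical analysis section:

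1. Make the main between-arm comparison a logistic model, or the planned GEE logistic model, adjusted for baseline accelerometer MVPA (continuous, log scale), centre and ADT duration. Report it as a marginal risk difference with its interval, so that the result stays on the scale of the raw percentages; an adjusted odds ratio would target a different quantity.
2. Keep the percentages by arm and window as description.
3. Include baseline accelerometer MVPA in every model for predictors of adherence.

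An analysis restricted to men below 150 min on baseline accelerometry is optional, as a sensitivity analysis only. The eligibility criterion and the 150-minute endpoint stay as they are.

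The cost is analysis wording, with no new data collection. The log scale needs a stated rule for a recorded value of zero. Men without a valid baseline accelerometer week also need a rule: a missing indicator is adequate for the randomized comparison, and imputation is preferable in the predictor models.
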